#### Study cohort

We will select a study cohort from the CPRD Aurum to investigate objectives 1–3. We will identify and extract the records in the primary care and HES dataset for all patients with a diagnosis of SMI (hereafter *exposed*) and who are eligible for data linkage. Diagnostic Read codes, which are the standard clinical codes used in UK general practice, will be used to identify an SMI diagnosis. We will also use codes according to the International Classification of Diseases version 10 (ICD-10) from the HES data. The date of the first SMI Read code will be used as the index date, which is the earliest date that an exposed patient may enter the study. From the study cohort, a subcohort of patients will be selected to investigate objective 4. To enter the subcohort, the exposed patient needs a recorded BMI ≥25 kg/m^2^ at any time after the index date. All information will be extracted for the period 01 January 1998 to 31 October 2020—the earliest and latest dates respectively that data are available.

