#### Exclusion criteria

Patients will be excluded from the cohort(s) if they: have less than 1 year of active data in their participating practice before the index date; and/or who have a Read code for coronary heart disease, congestive heart failure or cardiomyopathy, and/or stroke before the index date. A flow diagram will present the selection and exclusion (with reasons where possible) of patients in the study.

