#### Duration of follow-up

Patients will be followed up in the database from their index date until the earliest of the following: date of death; date of outcome of interest; date of leaving the participating practice; date of the latest download of data; or the end of the study follow-up period (ie, up to 22 years).

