#### Comparison group

The unexposed represents the counterfactual and will include patients without an SMI Read code ever (hereafter *unexposed*) drawn from the source population. Up to four unexposed matches will be selected at baseline only if they have a qualifying weight Read code within±one year of the index date to the exposed in which they are matched. The matching variables include: age, sex, practice and calendar time. All weight Read codes will be extracted.

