### Sample size calculation

The estimated median follow-up time for the *exposed* with a weight Read code in their record in the 1 year *before* the index date is 3.2 years (mean: 4.6), which is based on our feasibility work for this project. We assumed a 1% annual incidence rate of CVD meaning 3% of the study population would develop CVD over the 3.2 years of follow-up.^30^ We also assumed a relative risk (RR) of 1.3 for CVD in the *exposed* versus *unexposed*.^31^ The n ratio was set at 0.25, which achieved the best balance between statistical power and data cost. Our calculation suggested a minimum sample size of n=3907 at 80% power to detect an RR of 1.3, alpha <0.05%. Our feasibility estimates indicate that there are 135 870 patients with SMI in CPRD Aurum, meaning the study is sufficiently powered to detect small effects.

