### Statistical analysis

Analyses will be conducted in Stata using an estimation approach. We do not intend to impute missing data. The entry date into the analysis is the index date. The outcome date is the earliest of: (1) the date of death or (2) date of diagnosis of the outcome of interest. For objectives 1 and 2, we will use all repeated measures and run separate models for each analyses. For objective 3, we will use the first recorded diagnosis of the outcome of interest rather than recurrent events. Patients who do not have the outcome of interest will be censored at the earliest of: (1) date of death, (2) date of leaving the practice, (3) date of the latest download of data or (4) the study end date.

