Since the study is descriptive, any association observed would not imply an SMI diagnosis is causative of adverse physical health outcomes. However, we might assume the greater the magnitude of the observed association the less likely it is due to bias and more likely due to a causal process.^32^ Furthermore, diet and physical activity are unmeasured confounders because they are unobserved in CPRD Aurum. Similarly, other unmeasured confounders like poverty may place people with SMI at increased risk of homelessness, which has consequences on healthcare access and provision. We address this potential confounding by linking to patient level IMD as a proxy measure of SES, but acknowledge this may not fully capture deprivation and leaves room for residual confounding. Moreover, information bias may be present since the CPRD Aurum relies on a GP recording of health outcomes. Furthermore, we can only examine primary care prescriptions. Any prescribing solely within secondary care may not be included as this was not historically routinely recorded in GP records. Thus, it is possible we will miss the first prescription(s). Finally, physical health checks are not always performed on random samples of the population, and it is possible that more regular testing is done on people with overweight and obesity. We expect that some patients will have incomplete information recorded. However, by determining what proportion of patients do not have appropriate information recorded, we can evaluate the scale of these problems, and highlight the need for improved recording for continuity of care between healthcare professionals.

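### A weight record within one year either side of index is an entry condition for the unexposed only, so controls are selected on being weighed and some carry immortal time

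*Protocol article*

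**What the plan says.** **Unexposed.** The Comparison group section says that up to four matches per exposed patient are "selected at baseline only if they have a qualifying weight Read code within±one year of the index date" of the patient to whom they are matched. The window therefore extends to one year after index.

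**Exposed.** The Study cohort section takes in "all patients with a diagnosis of SMI (hereafter *exposed*) and who are eligible for data linkage". The Exclusion criteria section removes patients who "have less than 1 year of active data in their participating practice before the index date" and those with earlier coronary heart disease, heart failure or cardiomyopathy, or stroke. Neither section mentions a weight record.

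**Time zero.** Duration of follow-up states: "Patients will be followed up in the database from their index date until the earliest of the following: date of death" or one of the other end points listed there. The Statistical analysis section confirms: "The entry date into the analysis is the index date". No delayed entry or landmark is described.

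**The one mention of a weight near index for the exposed.** The Sample size calculation gives median (3.2 years) and mean (4.6 years) follow-up for exposed patients "with a weight Read code in their record in the 1 year" before index. This describes feasibility work, and its window differs from the controls' window.

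**The concern.** Two separate selections act on the comparison group and not, in the same form, on the exposed.

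1. **Being weighed.** Every control has a weight record close to index; an exposed patient need not. The Discussion acknowledges that health checks are not made on random samples and that "it is possible that more regular testing is done on people with overweight and obesity". If weighed people differ in cardiovascular risk from unweighed people of the same age, sex, practice and calendar time, the controls no longer stand for the source population they are meant to represent.
2. **Surviving to be weighed.** A control who qualifies only through a weight after index cannot have died or left the practice before that date. The time from index to that weight counts as follow-up, yet no death can occur in it.

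Objective 3 (CVD incidence, CVD death and all-cause mortality from index) is the most exposed. No planned analysis removes either selection from the primary comparison, and controls who were never drawn cannot be restored at the analysis stage.

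**Working it through.** **Step 1. Eligibility and time zero side by side**

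| Rule | Exposed | Unexposed |
|---|---|---|
| Weight record needed to enter | No | Yes |
| Window | None | 1 year before to 1 year after index |
| Start of follow-up | Index | Matched index |
| Must survive past index to qualify | No | Yes, if the only qualifying weight is after index |

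**Step 2. The protocol's own sample size.** Inputs from the Sample size calculation: 3% CVD risk in the unexposed, RR 1.3 (so 3.9% in the exposed), ratio 0.25 (1:4) and 80% power. I used two-sided alpha 0.05, because the printed 0.05% does not reproduce the figure. The pooled risk is (0.039 + 4 × 0.03)/5 = 0.0318. Then

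n exposed = [1.960 × √(1.25 × 0.0318 × 0.9682) + 0.8416 × √(0.039 × 0.961 + 0.03 × 0.97/4)]² / 0.009² = (0.3845 + 0.1780)² / 0.000081 ≈ 3907.

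The stated 3907 is therefore the exposed group alone, with 4 × 3907 = 15,628 unexposed. As a share of the available SMI patients, 3907/135,870 = 2.9%.

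**Step 3. Immortal time, as an illustration.** Let f be the share of controls who qualify only by a post-index weight. The document does not give f. Further assumptions: those weights are spread evenly over year 1 (mean 0.5 year), the hazard is constant, and follow-up of length T is similar in both groups. The values 3.2 and 4.6 years are borrowed for T from the feasibility figures, which concern exposed patients with a weight before index.

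- Immortal share of control person-time: s = f × 0.5 / T
- Observed control death rate = true rate × (1 − s)
- A true rate ratio of 1.00 appears as 1/(1 − s)

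| f | T = 3.2 years | T = 4.6 years | Year 1 only (T = 1) |
|---|---|---|---|
| 10% | 1.016 | 1.011 | 1.053 |
| 25% | 1.041 | 1.028 | 1.143 |
| 50% | 1.085 | 1.057 | 1.333 |
| 75% | 1.133 | 1.089 | 1.600 |

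Example: f = 75% and T = 3.2 give s = 0.375/3.2 = 0.117, and 1/(1 − 0.117) = 1.133. All of the distortion lies in year 1.

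**Step 4. Direction by outcome**

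- *Death:* immortal time lowers the control rate, so SMI looks worse.
- *Non-fatal CVD:* an event between index and the weighing does not bar a control and may prompt the weighing, so the direction is uncertain.
- *Selection on being weighed:* if weighed controls carry higher risk, the contrast shrinks. This can oppose the immortal-time effect for fatal events.

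**The case against.** **The exposed may have been meant to have a weight record too.** The article is condensed, and the feasibility text hints at this. It is possible but not shown. Even then the windows would differ, and the post-index part would still apply to controls only.

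**Objectives 1 and 2 select the exposed as well.** This stands. These objectives model repeated measurements without imputation, so a patient with no measurement of an outcome contributes nothing to that model. A reader might infer that all of objectives 1–3 set an unselected SMI group against selected controls; that is too broad. What remains for objectives 1–2 is that the selection does not use the same window.

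**Controls are enriched for risk, so the CVD hazard ratio is biased to the null.** A reader might infer this from the Discussion, but the protocol says only that more regular testing of people with overweight and obesity is possible. One could assume that 40–60% of potential controls are weighed and carry 1.2–1.5 times the risk of the others, and so reduce a true HR of 1.30 to 1.04–1.21. Those inputs have no source in the document. The sum also ignores the planned matching and the adjusted Cox model, whose covariates include smoking, baseline BMI, lipids, blood pressure and glycaemia. Only risk left after adjustment would count.

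**A post-index weight would serve as baseline and hide early gain.** A reader might infer this too, but no section names that weight as baseline. The mixed model uses all measurements, with time and its interaction with SMI.

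**Selection is acknowledged and sensitivity analyses are planned.** The acknowledgement is general and mentions neither the one-sided rule nor the later window. Dropping outcomes within two years of the SMI code would cover the year-1 window if it were applied to controls from their matched date. It is aimed at reverse causality and leaves both the weighing rule and the primary analysis unchanged. The complete-data analysis does not align the entry windows either.

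**Conclusion.** The concern holds on the protocol's stated eligibility and time-zero rules. Controls are selected on being weighed and, where the only qualifying weight is after index, on surviving and staying registered until then. The exposed have no matching condition. Objective 3 is affected most.

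For mortality, the immortal-time component makes SMI look worse. Under the assumptions in the working, a null rate ratio would appear as about 1.01–1.13 overall and 1.05–1.60 within year 1. These figures illustrate a range of f and do not estimate the bias. Selection on being weighed may pull the other way, so the net direction for fatal CVD is not fixed, and that for non-fatal CVD is uncertain. Against a planning RR of 1.3, a distortion of unknown sign and possibly this size is enough reason to change the rule before controls are drawn.

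**What to change.** **Primary change.** State one weight-record rule in Study cohort and Comparison group, applied to both groups, with a window that ends at the (matched) index date. The 12 months up to and including index would suit, as it is close to the window used in the feasibility work.

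**Alternative.** If a post-index weight is to be allowed, start follow-up in both groups at the qualifying weight or at a one-year landmark.

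**Sensitivity analysis.** Report objective 3 without the weight requirement in either group. This should not replace the primary analysis: baseline BMI is an adjustment variable and the mediation analysis needs weight data, so dropping the rule outright trades one problem for another. It also needs controls without a weight record to be extracted, which adds data cost.

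**Cost.** Revised wording and fewer exposed patients. For objective 3 the stated 3907 exposed is 2.9% of the 135,870 available before other exclusions, so its stated power is very unlikely to be threatened. That calculation concerns CVD and does not show what objectives 1 and 2 can afford to lose; however, exposed patients with no measurement already drop out of those models.

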### Exposures

For all analyses, the exposure of interest is SMI. We will extract information on the study cohort up to censoring. Extracted information includes the diagnosis date and type, which will be grouped according to the two major SMI subgroups as classified by the ICD-10: F20-29 non-affective psychotic disorder (ie, schizophrenia, schizotypal and delusional disorders, psychosis not otherwise specified) and F30-39 affective psychotic disorder (ie, bipolar, manic, schizoaffective disorders, major depressive disorder with psychosis). Patients may have Read codes in the primary care data relating to both non-affective and affective psychotic disorders. These will be classified using the most recent Read code because we will assume that the latest diagnosis is the correct one. For example, it is common for diagnoses to be clarified over time from first episode psychosis to schizophrenia. Based on similar studies, instances where there are Read codes relating to both diagnoses at the same date will be coded under non-affective psychotic disorder.^25^ Data on individual prescriptions for psychotropic medication will be extracted from the primary care data from index date until censored.

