The factors underlying excess weight gain in people with SMI are multifactorial. Psychotropic drugs (ie, antipsychotics, antidepressants, mood stabilisers) are the mainstay treatment for the symptoms of psychosis and affect weight.^9^ Evidence from clinical trials has linked these drugs to rapid weight gain, but the long-term effects after a diagnosis are unclear.^9^ In one 11-year follow-up study of people with schizophrenia, increased CVD mortality was reported in people treated with quetiapine (adjusted HR: 1.41, 95% CI 1.09 to 1.82) and reduced CVD mortality in people treated with clozapine (adjusted HR: 0.74, 95% CI 0.60 to 0.91).^10^ However, these estimates may result from unmeasured confounding by socioeconomic and other demographic factors.^11^ Accordingly, a better understanding of the long-term impact of medication on weight change, cardio-metabolic risk factors, and incidence of and mortality from CVD is warranted.

Other factors that cause weight gain include unhelpful dietary patterns and physical inactivity. These behaviours are more common in people with SMI compared with the general population and may reflect the social disadvantage to which SMI contributes.^12^ In addition, the prevalence of smoking is estimated to be twice that in people with SMI compared with general population,^13^ and evidence shows people with schizophrenia smoke more cigarettes per day and more intensely than the general population of smokers.^14^ Other studies using polygenic risk scores for liability to schizophrenia have found no association between those scores and physical health outcomes except for conditions mediated through obesity and smoking.^15^ This suggests that the excess risk to people with SMI are modifiable.

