### Confounding

We have identified confounding variables using directed acyclic graphs (DAGs), which aims to theoretically formalise potential confounders, colliders and biasing relationships.^26^ The DAG for each objective is described in online supplemental material S1. The DAG for objective 1 shows one direct path from the exposure (ie, SMI) to the outcome (ie, weight change), and four indirect paths: via health behaviours (ie, alcohol use, smoking and diet), SES status, psychotropic medication, and healthcare access and provision. Diet and physical activity are latent variables in CPRD Aurum because they are unmeasured. There are three confounding paths: via age, sex and ethnicity.^27 28^ Thus, the minimally sufficient adjustment for the total effect of SMI status on weight is to adjust for age, sex, and ethnicity.

10.1136/bmjopen-2021-053427.supp1Supplementary data

Frequency matching will ensure our ability to adjust for confounding variables that include age, sex, and calendar year, and matching on practice will remove practice-specific variables. In addition, we will fully adjust our models by considering several covariates in the relationship between the exposure and outcome (see table 2). All categorical variables will be analysed using the natural reference category as the reference group. Data on individual prescriptions for psychotropic and cardio-metabolic medications will be extracted from the primary care data from index date until censoring. For psychotropic medications, drugs will be classified according to the British National Formulary. For objectives 2 and 3, we will assess the impact of weight gain on change in cardio-metabolic risk factors and incidence of CVD using mediation analysis to allow us to estimate the direct (unmediated) and indirect (mediated) effects of SMI on CVD risk and incidence. To do this, we will fit two regression models: one regressing the outcome on the exposure, adjusting for confounders and another regressing the mediator on the exposure and confounders using the Stata *Med4way* command to estimate mediated effects.^29^ For objective 4, we will assess the presence of confounding by comparing estimates with and without adjustment. We will use Read codes, which have been previously developed by our team, to identify outcome and covariate records.

**Table 2 T2:** Confounders

Confounders and covariates		Measures

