Health behaviours	Smoking status	Categorical (0=never; 1=ex-smoker; 2=current smoker (light: 1–9 cigarettes/day; moderate: 10–19 cigarettes/day; heavy: 20+ cigarettes/day)). This is coded in GP records. We will use the most recent recorded value of smoking status at the study start date.
	Alcohol use	Continuous (units per week). This is coded in GP records. We will use the most recent recorded value of alcohol use at the study start date.
Demographics	Socioeconomic status (SES)*	Categorical (quintiles)
	Ethnicity†	Categorical (white; Asian or Asian British; black or black British; other ethnic group, mixed)
	Sex†	Binary (0=male; 1=female)
	Age at study entry, in years	Continuous
Physical and/or medical factors	Baseline weight status (body mass index (BMI))	Categorical (normal weight (BMI 18.5–24.9 kg/m^2^); overweight (25.0–29.9); obese (30.0–34.9); severe obesity (35.0–35.9); morbid obesity (40.0–44.9)
	Psychotropic medication	Categorical (antipsychotics (first-generation and second-generation); antidepressants; mood stabilisers)
	Cardio-metabolic medication	Categorical (blood glucose lowering medications; antihypertensive treatments, statins)
We include the following additional variables for objectives 3 and 4 only		
CVD risk factors	Total cholesterol/HDL ratio	Continuous
	Systolic and diastolic blood pressure	Continuous
	Glycaemia	HbA1c/fasting blood glucose (FBG)

*This variable is grouped according to practice level Index of Multiple Deprivation. This is an indicator of material deprivation based on income; employment; health deprivation and disability; education, skills and training; crime; barriers to housing and services; and living environment. It is categorised as quintiles 1–5 with 1 being the most deprived and 5 being the least deprived.

†This variable is grouped according to recommendations by the UK Office for National Statistics.^33 34^

CVD, cardiovascular disease; GP, general practitioner; HbA1c, haemoglobin A1c; HDL, high-density lipoprotein.

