#### Primary analyses

For objectives 1 and 2, the outcome will be visually inspected by plotting trajectories of weight and cardio-metabolic risk factor change using all repeated measurements for patients with SMI versus patients without SMI. For these analyses, we will use a mixed-effects linear regression model including terms for SMI, time and their interaction to estimate regression coefficients with 95% CIs by SMI status. Models incorporating psychotropic medications will analogously include medication-time multiplicative interaction terms. We will include a random effect for individual and practice identifier to account for intra-class correlation resulting from common practice membership. Diagnostic tests will be conducted to confirm linear regression assumptions are met including linearity of residuals, residual normality using quantile–quantile (Q–Q) plots, and residual heteroscedasticity using residual versus fitted value plots. We will assess for exploratory subgroup effects by adding interactions (eg, by age, sex, ethnicity and SES) and, if significant, we will assess the strength of the associations in separate subgroups for clarity. For objective 2, we will model the association between weight and cardio-metabolic change using restricted cubic splines to allow for non-linear associations. For objective 3, we will use Kaplan-Meier survival estimates for the exposed and unexposed groups to estimate the distribution of time from index date to total and fatal CVD and mortality (all-cause). The statistical equivalence of the two curves will be examined using the log-rank test. This analysis will use a survival from index date between the exposed and unexposed groups using an adjusted Cox proportional hazards regression model with follow-up time as the timescale. Restricted cubic splines will be computed with five knots to visually explore non-linear associations between the exposure and the outcomes. For objective 4, we will use a Poisson regression examining person-time to estimate the rate at which patients who received weight management services over the study period in patients with SMI compared with patients who do not have SMI, adjusting for confounders and BMI.

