## Discussion

In the UK, the NHS Long Term Plan commits the health service to greater action on reducing inequalities for the most overlooked groups. This study responds to this national agenda by focusing on the major cause of death for people with SMI—cardiovascular disease. We plan to leverage the power of a large UK primary care database to provide new insight on how these actions may be achieved.

Our results will estimate weight change, its risk factors including psychotropic medication, and its management in primary care as a preventative target for CVD. This could inform medication choice for people with SMI and clinicians, particularly if there are meaningful differences between drugs. In addition, our results will estimate the change in cardio-metabolic factors in people with SMI relative to those without SMI. This will be valuable to policy-makers because these are key risk factors for CVD that are being addressed through the NHS Long Term Plan. Furthermore, identifying the factors underlying the higher incidence of CVD will help us understand the degree to which these factors are valuable therapeutic targets. Lastly, understanding whether people with SMI are being offered support to manage their weight will inform national initiatives to overcome therapeutic nihilism. It is also important to understand whether there are differences in response between people with SMI and the general population, which would inform us about whether interventions need to be tailored to people with SMI for more personalised care. Ultimately, the results will offer a foundation to assess the degree to which the current focus on CVD prevention in people with SMI is having clinical benefits.

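### Medication-by-time terms come from models built for SMI as the exposure, so they are not adjusted for a confounder set chosen for medication and cannot support the suggestion that results may guide drug choice

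*Protocol article*

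**What the plan says.** The Exposures section is explicit: "For all analyses, the exposure of interest is SMI". All four objectives at the end of the Introduction are comparisons of people with and without SMI.

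The Confounding section describes the causal diagram for objective 1 as having "four indirect paths: via health behaviours (ie, alcohol use, smoking and diet), SES status, psychotropic medication, and healthcare access and provision". Medication is therefore one of the routes by which SMI acts on weight. From that diagram the protocol concludes that "the minimally sufficient adjustment for the total effect of SMI status on weight is to adjust for age, sex, and ethnicity". It adds that "we will fully adjust our models by considering several covariates in the relationship between the exposure and outcome", and points to Table 2. There, psychotropic medication is coded as "Categorical (antipsychotics (first-generation and second-generation); antidepressants; mood stabilisers", that is, by class.

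Primary analyses, for objectives 1 and 2, specifies SMI, time and their interaction, and then says: "Models incorporating psychotropic medications will analogously include medication-time multiplicative interaction terms".

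The Discussion expects the study to estimate weight change and its risk factors, naming psychotropic medication among them, and continues: "This could inform medication choice for people with SMI and clinicians, particularly if there are meaningful differences between drugs".

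**The concern.** A covariate set that suffices for the effect of SMI does not thereby suffice for the effect of a drug. If SMI is the exposure, medication lies downstream of it, and the question is which common causes of SMI and weight need control. If medication is the exposure, the question is why this patient received this class at this time. SMI type, the weight course up to the prescription and the drugs already tried are all plausible reasons, and each may also bear on later weight.

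Coefficients for medication by time in the SMI models are covariate coefficients. Reading them as differences between treatments mixes drug effects with the reasons for prescribing. A class given more often to patients who are already gaining weight could look worse than it is, and a class given mainly to patients with a different diagnosis could look better or worse. This matters because the drug reading is the one the Discussion offers to patients and clinicians.

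**Working it through.** The point concerns what is estimated and which confounders are chosen for it, so the main check sets the sections side by side.

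1. **Exposure and diagram.** The exposure is SMI throughout (Exposures; objectives). There is one diagram per objective (Confounding), and each objective is an SMI comparison. The article names no medication contrast, comparator group or medication-specific adjustment set.

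2. **Role of medication.** It is an indirect path in the objective 1 diagram, a class-level covariate in Table 2, and an interaction with time in Primary analyses.

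3. **What Table 2 holds that could influence prescribing.** Age, sex, ethnicity, deprivation quintile, smoking, alcohol, baseline BMI category and cardio-metabolic medication. The mixed model also contains SMI status. Part of the confounding of drug choice is therefore covered.

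4. **What Table 2 does not hold.**
   - SMI type. It is extracted and grouped under Exposures but is not listed as a covariate.
   - Weight or weight trend when the drug is prescribed. Baseline BMI category is fixed at entry, whereas prescriptions are collected from index to censoring and follow-up can last up to 22 years.
   - Previous psychotropic use.

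5. **Coding against claim.** The Discussion speaks of differences between drugs. Table 2 codes classes, so as categorised the terms could not separate individual drugs. Finer coding would not by itself remove confounding by indication.

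6. **Limitations.** The closing paragraph of the Discussion says an association would not show that an SMI diagnosis is causal. It lists unmeasured diet, physical activity and poverty, incomplete recording, and missing secondary-care prescribing. It does not mention confounding by indication.

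**The plan's own figure.** The only planning calculation is for CVD by SMI status. Inputs from Sample size calculation: unexposed risk p0 = 0.03, RR 1.3, so p1 = 0.039; four unexposed per exposed; 80% power. Two-sided alpha is taken as 5%. The pooled risk is 0.8 × 0.03 + 0.2 × 0.039 = 0.0318. Then

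n exposed = [1.960 × √(0.0318 × 0.9682 × 1.25) + 0.842 × √(0.039 × 0.961 + 0.03 × 0.97 / 4)]² / 0.009² ≈ 3907.

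This reproduces the stated 3907, with 4 × 3907 = 15,628 unexposed. It concerns SMI against no SMI and neither supports nor weakens a drug contrast.

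**Illustration of the mechanism; every input is assumed.** 200,000 simulated people, 20% with SMI. Severity is standard normal within SMI and zero otherwise. Log-odds of prescribing = −3 + 3 × SMI + g × severity. Outcome = 1.0 × drug + 0.5 × SMI + 1.0 × severity + noise with SD 3. The true drug effect is 1.0.

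| g (log-odds of prescribing per SD of severity) | Drug coefficient, model with SMI and drug | With severity added |
|---|---|---|
| 0 | 0.98 | 0.98 |
| 1 | 1.45 | 0.99 |
| 2 | 1.69 | 0.98 |

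Adjusting for SMI status leaves the confounding in place; adjusting for the reason for prescribing removes it. The simulated outcome is a single value and not a slope over time, and the other Table 2 covariates are left out. The table therefore shows a direction of reasoning and does not size the bias in this study.

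**The case against.** The strongest reply is that no drug comparison is an objective. The exposure is defined clearly and consistently, medication is a covariate, and the medication-choice remark is one conditional sentence in a discussion. On this view only wording is at issue. Much of that stands: the definition of the exposure is not an error, and the SMI estimates are not challenged here. But the sentence states a clinical use for results that no described analysis supports, and the Introduction also gives the long-term impact of medication as a reason for the study.

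Four stronger readings are tempting, and the document does not support them.

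- A reader might infer that the medication terms are adjusted for none of their confounders. Table 2 contradicts this, as step 3 shows.
- A reader might infer that the plan repeats the fault it finds in earlier drug estimates. The Introduction says of those: "However, these estimates may result from unmeasured confounding by socioeconomic and other demographic factors". That is socioeconomic and demographic confounding, which the plan addresses through deprivation, ethnicity, age and sex. Confounding by indication is a different matter that the Introduction does not raise.
- A reader might infer that users with and without SMI are pooled under one drug slope. This is the natural reading of Primary analyses, but neither the population for the medication models nor the coding of medication (baseline, ever or time-varying) is stated, and an article may leave that to the full plan.
- A reader might attach kilograms to the bias. If 20% to 40% of users of one drug had switched to it after gaining 2 to 4 kg on another, 0.20 × 2 = 0.4 kg to 0.40 × 4 = 1.6 kg would be at issue. All inputs are assumed. The gain would pass into the second drug's slope only under some codings, such as ever-use; with time-varying coding it falls in the first drug's person-time. A switch within a class yields no contrast under Table 2 at all.

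The supplementary diagrams are not shown. They are described as one for each objective, so a separate medication diagram is not to be expected, though it cannot be excluded.

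**Conclusion.** The point holds in a limited form. The medication-by-time terms are not adjusted for a confounder set chosen for medication, and SMI type, weight or weight trend at prescribing and previous psychotropic use are absent from Table 2. These terms cannot carry the suggestion in the Discussion that the results may guide medication choice, and the stated limitations do not warn the reader of this.

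The conclusion rests on the diagrams following the SMI objectives, as the text describes, and on Table 2 being the full covariate list. The direction and size of any bias are unknown. What changes is what the study may claim about drugs; what it may claim about SMI does not change.

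**What to change.** Three changes of wording cost almost nothing:

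1. State in Primary analyses that medication-by-time terms are for adjustment or are exploratory, and are not estimates of comparative drug effects.
2. Remove the medication-choice sentence from the Discussion, or limit it to generating hypotheses at class level.
3. Add confounding by indication to the limitations.

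If drug contrasts are to be reported, fit them within exposed patients only, by class. Adjust for SMI type, the last weight before the prescription and psychotropic use recorded since index. SMI type is already extracted, and the protocol says that all weight codes will be. Because Exposures assigns type from the most recent code, type as coded up to the prescription would be the better covariate.

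The price is fewer patients and wider intervals. First prescriptions issued in secondary care may still be missed, as the Discussion acknowledges.

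A full comparison of new users of one class with new users of another is optional and not clearly cheap. Psychotropic prescriptions are to be extracted from the index date onward, so a drug-free period or treatment history for people who start around diagnosis may need earlier records.
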